### Interim analysis and monitoring

Because this is a short-term study with a 2-year follow-up period, we will not conduct interim analysis. However, the safety of PDD-EBTUR will be independently evaluated by the Safety Monitoring Committee when:
i)A critical modification of the study protocol is requiredii)Any serious adverse event associated with this surgical procedure occursiii)A critical problem is observed while monitoringiv)The principal investigator needs the judgment of this committee

Protocol amendments based on the judgment of Safety Monitoring Committee, regarding eligibility criteria, outcomes, and analyses, will be released to relevant parties (investigators, the Ethics Committee of Nara Medical University, trial participants, and trial registry).

Principal Investigator reports about implementation of the clinical trial, data correction, adverse events, and protocol deviation and violation to the data monitoring committee (DMC), at least when the first patient is enrolled and annually. The DMC is composed by the Clinical Research Center of Nara Medical University, which evaluate whether the study is implemented in compliance with the study protocol and whether the data are appropriately corrected according to a pre-arranged monitoring plan, independently from the clinical trial team. The DMC has no potential conflict of interest. The Trial Steering Committee was not set up in this clinical trial.

### Statistical analysis

The full analysis set (FAS) population will be analyzed for both the primary endpoint (2-year RFS rate) and survival outcomes (Fig. 3; RFS after 2 years, progression-free survival, progression-free rate, upper urinary tract cancer-free survival, metastasis-free survival, cancer-specific survival, and overall survival), and the per protocol set (PPS) population will be analyzed for the other secondary endpoints. A two-sided *P* value of less than 0.05 will be considered to be statistically significant.

To compare the PDD-cTURBT and PDD-EBTUR groups, descriptive statistical analysis will be performed for all study variables. To assess the prognostic impact of the surgical procedure and clinicopathological parameters, event-free survivals will be estimated using the computing risks model; this model considers patients who die of other causes (competing events) before recurrence or progression. The Gray test and Fine-Gray subdistribution hazard regression will be applied to the primary endpoint and the survival outcomes at the secondary endpoints to compare the groups and to calculate the hazard ratio. In addition, a sensitivity analysis of the primary endpoint will be performed using the log-rank test and Cox proportional hazard regression analysis. The amount of change in other post-operative observations over time will be analyzed using the repeated measures analysis of variance (ANOVA), Wilcoxon signed-rank sum test, or Mann-Whitney *U* test. For analyses of cross-sectional measures for continuous and categorical variables, the Mann-Whitney *U* test and Fisher’s exact test, respectively, will be used. A subgroup analysis will be performed to examine whether effects of the intervention differ between subgroups according to the characteristics of patients.

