**Fig. 3 Fig3:**
[figure not shown]
Secondary endpoints of the FLEBER study. Abbreviations: CTCAE, Common Terminology Criteria for Adverse Events; SF-8, Short Form-8 health survey; EORTC, The European Organization for Research and Treatment of Cancer; FACT-BL, Functional Assessment of Cancer Therapy-Bladder; NPRS, numerical pain rating scale; VAS, visual analog scale; FPS, faces pain scale; IPSS, International Prostate Symptom Score; OABSS, overactive bladder symptom score

Patient data will be collected before the surgery, and 1, 3, 6, 9, 12, 15, 18, 21, and 24 months after the surgery (Fig. 4). Recurrence was defined as pathologically proven urothelial carcinoma. Progression was defined as a recurrent disease with upstaging from Ta to T1 or invasion into the muscularis propria (≥ T2), positive regional lymph node, and/or distant metastases. After 24 months of follow-up, patients will be followed-up every 6 months for 3 years, and annually thereafter. To improve monitoring adherence, the clinician will take time to explain about need for post-operative surveillance examination and encourage the participants to undergo routine cystoscopy and urine cytological examination.

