**Fig. 4 Fig4:**
[figure not shown]
Intervention and assessment schedule for the FLEBER study according to the Recommendations for Interventional Trials (SPIRIT). Follow-up visits and data collection should occur approximately 1, 3, 6, 9, 12, 15, 18, 21, and 24 months from the surgery. Patients will complete a set of questionnaires at every visit, and follow-up information may be collected via medical charts. The Case Report Form will include information regarding past history, concomitant medications, and any medications taken after the treatment. Chest–abdomen–pelvis computed tomography (CT) and/or magnetic resonance imaging (MRI) should be performed for TNM classification. X, mandatory; *hemoglobin, hematocrit, white blood cell count and fractions, platelet count; **aspartate transaminase (AST), alanine transaminase (ALT), γ-glutamyl transpeptidase (γ-GTP), total bilirubin, alkaline phosphatase (ALP), lactate dehydrogenase (LDH), total protein, albumin, serum creatinine, uric acid, total cholesterol, low-density lipoprotein (LDL)-cholesterol, high-density lipoprotein (HDL)-cholesterol, triglyceride, C-reactive protein (CRP), calcium, phosphorus, potassium, chloride; ***Urine dipstick test (specific gravity, pH, protein, glucose, bilirubin, urobilinogen, ketone body, and occult blood) and urine sediment test; ^†^3 days and nights record. Patients pick days that will be convenient for them to measure and record everything; ^††^pain scale measures: numerical pain rating scale (NPRS), visual analog scale (VAS), and faces pain scale (FPS); ^†††^according to the Common Toxicity Criteria for Adverse Events (CTCAE v 5.0) translated into Japanese; ^††††^questionnaires: SF-8™, EORTC QLQ-C30, and FACT-BL. Abbreviations: BW, body weight; BT, body temperature; BP, blood pressure; ECOG-PS, Eastern Cooperative Oncology Group-performance status scale; PDD, photodynamic diagnosis; EBTUR, en bloc transurethral resection of bladder tumor; cTURBT, conventional transurethral resection of bladder tumor; QOL, quality of life; IPSS, International Prostate Symptom Score; OABSS, overactive bladder symptom score

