### Determining the target sample size

To date, we have conducted several observational studies on the oncological outcomes of NMIBC patients treated using TURBT with or without intravesical treatment [1, 20–23]. Our study subjects include patients with low- or intermediate-risk NMIBC, who were treated with TURBT followed by IPIC (with no further adjuvant treatment) and who were eligible for the pilot analysis. We observed that the 2-year RFS rate in this subset was 77.3% and most of the recurrent tumors were diagnosed within 2 years after TURBT (Fig. 5). Based on this observation, we selected the 2-year RFS rate after TURBT as the primary endpoint of this trial. In previous clinical trials, the 2-year RFS survival rate after TURBT with IPIC ranged from 65 to 85% in patients with low- and intermediate-risk NMIBC [18, 24–26].

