**Fig. 5 Fig5:**
[figure not shown]
Recurrence-free survival curve after TURBT and immediate postoperative intravesical chemotherapy in patients with low- or intermediate-risk NMIBC. The analysis was based on our historical dataset, which included data from more than 1500 patients with NMIBC. Thirty-four patients were included in order to obtain the recurrence-free survival curve. Abbreviations: RFS, recurrence-free survival; TURBT, transurethral resection of bladder tumor; IPIC, immediate postoperative intravesical chemotherapy; NMIBC, non-muscle invasive bladder cancer

The required sample size was determined to test our null hypothesis of superiority in 2-year RFS rate after surgery. We hypothesized that PDD-EBTUR will suppress the risk of recurrence by 75%, yielding a 2-year RFS of 80% in the PDD-cTURBT group and by 95% in the PDD-EBTUR group. We calculated the sample size using EZR 1.37 (Saitama Medical Center, Jichi Medical University, 2018). To provide 80% power (β = 0.20) and an α level of 0.05 (two-sided), 48 patients are required in each arm with 3-year registration period and 2-year tracking period years. Assuming that 70% of patients would be diagnosed pathologically with Ta low-grade tumor without concomitant CIS and that the rate of dropout before the completion of the two-year follow-up would be approximately 10%, we plan to enroll 80 patients initially in each arm. Therefore, a total of 160 patients with clinically Ta-T1N0M0 bladder cancer will be enrolled and allocated by computer-aided randomization to either the PDD-cTURBT or PDD-EBTUR group (Fig. 1). Target sample size would be reached according to our annual record of surgery.

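### The primary endpoint is a 2-year rate, but the primary test has no stated 24-month horizon, and the 48 per arm gives 80% power only if events after month 24 are counted

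*Protocol article*

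**What the plan says.** Under Determining the target sample size the article states: "we selected the 2-year RFS rate after TURBT as the primary endpoint of this trial". The hypothesis matches: "The required sample size was determined to test our null hypothesis of superiority in 2-year RFS rate after surgery". The calculation assumes 2-year RFS of 80% (conventional resection) against 95% (en bloc). It concludes: "To provide 80% power (β = 0.20) and an α level of 0.05 (two-sided), 48 patients are required in each arm", on a design described as a "48 patients are required in each arm with 3-year registration period and 2-year tracking period years" calculation.

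Under Statistical analysis the primary endpoint is again labelled the 2-year RFS rate, and "The Gray test and Fine-Gray subdistribution hazard regression will be applied to the primary endpoint". In addition, "a sensitivity analysis of the primary endpoint will be performed using the log-rank test and Cox proportional hazard regression analysis". RFS beyond two years appears separately among the secondary survival outcomes. No censoring at month 24 and no comparison of rates at a fixed time is given.

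Surveillance does not stop at two years: "After 24 months of follow-up, patients will be followed-up every 6 months for 3 years, and annually thereafter" (Follow-up, data collection, and data protection). Trial status gives recruitment from August 2020 to July 2023 and the end of data collection in July 2025.

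**The concern.** The endpoint is a quantity at one time point. The Gray test, Fine-Gray regression, log-rank test and Cox model all compare curves or hazards over whatever follow-up enters the analysis. Which follow-up enters is therefore part of the definition of the primary result, and the article does not say. With only about 12 to 20 expected events, that choice could decide significance. The sample-size statement does not settle it: its accrual and tracking periods suggest a calculation over all follow-up, while the hypothesis it serves is about two years. If so, endpoint, test and stated power cannot all be right together.

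**Working it through.** **Inputs** (Determining the target sample size): 2-year RFS 80% and 95%; two-sided α 0.05; power 80%; 3-year registration plus 2 years, so analysis at 5 years; 70% evaluable; 10% dropout; 80 enrolled per arm. Assumed: exponential recurrence times, uniform accrual, no competing deaths.

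**Hazards.** λ₁ = −ln(0.80)/2 = 0.1116 and λ₂ = −ln(0.95)/2 = 0.0256 per year. Mean λ̄ = 0.0686, difference 0.0859, ratio 0.23.

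**Formula (Lachin-Foulkes).** n per arm = {[1.96·√(2φ(λ̄)) + 0.842·√(φ(λ₁)+φ(λ₂))] / (λ₁−λ₂)}², where φ(λ) = λ²/P(λ) and P(λ) is the probability of an observed event.

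**1. The plan's own figure, all follow-up (2 to 5 years).** P(λ) = 1 − (e^(−2λ) − e^(−5λ))/(3λ) gives 0.3201, 0.0856 and, at λ̄, 0.2121. Then φ = 0.03889, 0.00768 and 0.02219, and n = [(0.4129 + 0.1816)/0.0859]² = 47.9, so 48. The stated figure is reproduced.

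**2. Same formula, stopped at 24 months.** P = 0.20, 0.05 and 0.1282; φ = 0.06224, 0.01316 and 0.03671; n = [(0.5311 + 0.2311)/0.0859]² = 78.7, so 79. A direct comparison of 80% with 95% (two proportions, no continuity correction) needs 76. Two-sided variants limited to 24 months range from 58.1 (Schoenfeld) to 88 (two proportions, continuity-corrected); none gives 48.

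**3. Where the events fall.** With 48 per arm: all follow-up 48 × (0.3201 + 0.0856) = 19.5 events; to 24 months 48 × (0.20 + 0.05) = 12. Share after month 24 = 1 − 0.25/0.4057 = 38%.

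**4. Power at 24 months.** By formula, 59% (Lachin-Foulkes) to 61% (two proportions) with 48 per arm. With the 80 × 0.70 × 0.90 = 50.4 evaluable per arm that the enrolment target yields, 61% to 63%. Simulation with 48 to 50 per arm gives about 64% to 66%.

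**5. What the horizon does to the test.** Simulated log-rank test, 48 per arm (without competing deaths the Gray test behaves like it):

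| Scenario | Rejects, all follow-up | Rejects, cut at 24 months |
|---|---|---|
| 80% v 95% at 2 years, constant hazards | 85% | 64% |
| 80% v 95%, then equal hazards at the control rate (assumed) | 35% | 63% |
| 80% v 95%, then equal hazards of 0.02 per year (assumed) | 53% | 64% |
| 80% in both arms at 2 years, diverging later (assumed) | 14% | 5% |

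The last row shows that the whole-follow-up test can reject when the 2-year rates are equal. The two middle rows show that it can also miss a 2-year difference that the 24-month analysis would find more often.

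**6. Enrolment equivalents.** 48/(0.70 × 0.90) = 76.2, rounded up in the plan to 80. For 76 to 79 evaluable: 76/0.63 = 120.6 and 79/0.63 = 125.4, so about 121 to 126 enrolled per arm.

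**The case against.** The best counter-argument is that a 24-month cut is implied. The Gray test is applied to an endpoint named as a 2-year rate in the same section, RFS beyond two years is a separate outcome, Interim analysis and monitoring calls this a study with a 2-year follow-up period, and the abstract sets 3-monthly monitoring for two years. An exact censoring rule is also detail that a fuller analysis plan may hold.

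Much of this stands. A reader might infer that the primary test certainly uses events after two years and so fails to test its endpoint. The documents do not support that: they leave the horizon open, and the 24-month reading is a fair one. A reader might also infer that using all follow-up must raise the power. That holds only if the hazards stay roughly proportional after month 24, which the article does not show. Its remark that most recurrences in the historical series came within two years does not settle the later pattern.

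The objection does not rescue the sample size. On the 24-month reading, 48 per arm does not give 80% power, and a censoring rule in an unseen document would not change that statement. Nor is it a complete answer that whole-curve tests are usual for RFS: they suit an endpoint of time to recurrence, whereas this one is a rate at two years.

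**Conclusion.** The point holds as an inconsistency between endpoint, test and stated power, whichever horizon was meant. If the primary analysis uses all follow-up, the stated 80% is reproduced (simulation at 48 to 50 per arm gives about 85-87%), but under constant hazards some 38% of the events come after month 24 and the P value does not belong to the 2-year rate. If it stops at 24 months, the P value is close to the endpoint, but power is about 59-66% instead of 80%, and about 76-79 evaluable patients per arm would be needed.

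The figures rest on the plan's own 80% and 95%, exponential times, uniform accrual and no competing deaths. The reversal of power under equal late hazards depends on assumed scenarios and shows only that the direction is not fixed. It should be corrected before analysis. It does not make the trial uninterpretable.

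**What to change.** In Statistical analysis, state that the primary comparison covers recurrences up to and including those found at the 24-month cystoscopy. Tying the horizon to that visit suits a schedule in which "Follow-up visits and data collection should occur approximately 1, 3, 6, 9, 12, 15, 18, 21, and 24 months from the surgery". Name one deciding test: for example, the difference in 24-month cumulative incidence of recurrence with its 95% confidence interval, with the Gray test censored at that visit as supportive. Even when cut, the Gray test compares curves over 0 to 24 months and not the rate at 24 months, so the text must say which result decides. Keep the whole-follow-up Gray and Fine-Gray analysis for the secondary outcome.

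In Determining the target sample size, restate the power for that horizon as about 60-65% with the planned enrolment. Keeping 80% would instead mean about 121 to 126 enrolled per arm. The other coherent route is to redefine the primary endpoint as time to recurrence over all follow-up, which fits the existing 48 but gives up the 2-year rate as the declared endpoint.

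The recommended change costs a few sentences and no new data. Its downside is a less favourable stated power.

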One, 3, and 6 months after the surgery, the 24-h urinary frequency, total voided volume, and mean voided volume will be recorded on a frequency volume chart for 3 days [19]. Postoperative pain intensity will be assessed using the numerical pain rating scale, visual analog scale, and faces pain scale. The assessment includes patient-reported outcomes (PROs) such as the SF-8™, EORTC QLQ-C30, FACT-BL, International Prostate Symptom Score (IPSS), and overactive bladder symptom score (OABSS). The postoperative observational evaluation such as PROs can be discontinued upon participant request. The data will be documented in specific Case Report Forms for genitourinary adverse events (AEs) and other possible AEs using the Common Toxicity Criteria for Adverse Events (CTCAE v 5.0). AEs strongly related to the intervention of PDD-cTURBT or PDD-EBTUR are listed as follows: “Intraoperative urinary injury,” “Cystitis noninfective,” “Urinary tract infection,” “Dysuria,” “Hematuria,” “Bladder perforation,” “Urinary frequency,” “Urinary incontinence,” “Urinary retention,” “Urinary tract pain,” and “Urinary urgency.” Any other potential AEs are recorded and grouped into “related AEs” or “unrelated AEs.” When serious AEs occur, investigators report to the Safety Monitoring Committee.

[name] and [name] (Nara Prefecture General Medical Center) are members of data management team. They are not involved in participant-facing elements of the clinical trial. They are responsible for the data entry from medical charts, data security, and storage, including any related processes to promote data quality such as data double-checking to central data monitoring. To protect the patient personal information, unique identification codes (FLEBER IDs) will be assigned to all patients. All the data will be protected in password-accessible electronic data files on secure servers before, during, and after the trial, and only investigators will be able to access the files. All data and documents will be deleted and discarded 5 years after the end of the trial, unless the data are being used for another study.

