Functional patient-reported outcomes after TURBT, especially EBTUR, have been rarely investigated. Maximal effort should be made to mitigate postoperative urinary symptoms and deterioration of the QOL. A previous study demonstrated that patients with NMIBC are affected psychologically during the period between initial diagnosis using cystoscopy and TURBT [27]. Our previous report focused on the difference in the worsening of urinary symptoms and deterioration of health-related QOL between the EBTUR and cTURBT groups. The score of the daytime frequency (IPSS 2) increased only in the EBTUR group, but not in the cTURBT group [15]. We speculated that the resection of deeper layers of the bladder wall, the wider range of the bladder mucosa, and the longer operative time for the EBTUR group compared to the cTURBT group might be associated with the difference in the worsening of urinary symptoms. Moreover, QOL assessment revealed a decrease in emotional and mental scores among patients in the EBTUR group but not among patients in the cTURBT group. Presently, we cannot draw a conclusion regarding the difference between EBTUR and cTURBT. We plan to perform multiple assessments of the functional outcomes. Therefore, the present RCT will elucidate the true clinical value of EBTUR.

Successful management of NMIBC depends on complete resection and accurate pathological diagnosis. The goal of this prospective, single-center RCT is to determine the potential benefit of PDD-EBTUR followed by IPIC in patients with low- or intermediate-risk NMIBC who undergo TURBT. Ultimately, our findings will lead to the development of better interventions and potentially change the standard of care.

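### Secondary patient-reported, symptom, pain and voiding outcomes need one named, baseline-adjusted between-arm analysis; the listed tests include one that cannot compare arms, one that drops incomplete patients and one that leaves precision unused

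*Protocol article*

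**What the plan says.** The Statistical analysis section of the protocol article treats the longitudinal non-survival outcomes in one sentence. Its subject is "The amount of change in other post-operative observations over time". The methods are then given as a list of three: this change "will be analyzed using the repeated measures analysis of variance (ANOVA), Wilcoxon signed-rank sum test, or Mann-Whitney". The Follow-up section describes patient-reported outcomes in similar terms, so the sentence is most naturally read as covering SF-8, QLQ-C30, FACT-BL, IPSS, OABSS, the three pain scales and the frequency volume chart. The article gives no other analysis of change for them.

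The same section sets the population: "and the per protocol set (PPS) population will be analyzed for the other secondary endpoints".

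On the schedule, the Follow-up section says "Patient data will be collected before the surgery, and 1, 3, 6, 9, 12, 15, 18, 21, and 24 months after the surgery", and the Fig. 4 legend adds "Patients will complete a set of questionnaires at every visit". Voiding charts have a shorter schedule: "One, 3, and 6 months after the surgery, the 24-h urinary frequency, total voided volume, and mean voided volume will be recorded". The Abstract confirms that the charts, pain scales and quality-of-life questionnaires are also collected before surgery, so a baseline exists.

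On missing data, the Follow-up section states: "The postoperative observational evaluation such as PROs can be discontinued upon participant request". The sample-size section expects about 10% dropout over two years.

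**The concern.** The three tests answer different questions, and the sentence does not say which one carries the comparison of arms.

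- **Wilcoxon signed-rank** compares before with after in the same patients. It gives a result for each arm but no test of one arm against the other.
- **Repeated-measures ANOVA** in its classical form needs a value at every visit. Patients may stop the questionnaires on request, so those who remain may be a selected subset.
- **Mann-Whitney on change** does compare the arms, but it makes no further use of the baseline score as a covariate.

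The Discussion calls functional outcomes after EBTUR rarely studied and relies on this trial to clarify them. If within-arm results were read as a comparison, the trial could report an arm difference that does not exist. If incomplete patients were dropped and baseline left unadjusted, it could miss a real one.

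**Working it through.** The article gives no target figure for these outcomes. Its one calculated figure, 48 per arm for 2-year RFS, reproduces: 47.9 by the Lachin-Foulkes formula with exponential survival, RFS of 80% and 95%, uniform 3-year accrual, 2-year minimum follow-up, two-sided 5% and 80% power. Nothing below depends on it.

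**Inputs from the article:** 80 patients enrolled per arm; about 10% dropout; nine post-operative questionnaire visits; three post-operative voiding-chart visits; two-sided 5% significance. **Assumptions:** missed-visit rates, baseline correlations, size of change and size of effect. The article gives none of these, so ranges are shown.

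**1. Signed-rank read across arms.** Suppose both arms truly change by the same amount and each within-arm test has power p. Then P(exactly one arm significant) = 2p(1 - p).
- Maximum, at p = 0.5: 2 x 0.5 x 0.5 = 50%.
- With no change in either arm, p = 0.05: 2 x 0.05 x 0.95 = 9.5%.

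Simulation with 72 per arm, no arm difference, 4,000 trials per row:

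| Common change (SD of change) | Exactly one arm significant, signed-rank | Between-arm Mann-Whitney on change significant |
|---|---|---|
| 0.2 | 46% | 4.8% |
| 0.3 | 43% | 5.0% |
| 0.4 | 16% | 5.1% |

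The between-arm test holds its 5% level; the within-arm pattern does not.

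**2. Patients kept by classical repeated-measures ANOVA.** Complete fraction = 0.9 x (1 - m)^9, where m is the chance of missing any one post-operative visit, independent across visits.

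| m | Complete fraction | Of 80 per arm |
|---|---|---|
| 0 | 0.900 | 72 |
| 2% | 0.750 | 60 |
| 5% | 0.567 | 45 |
| 10% | 0.349 | 28 |

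Voiding charts at m = 5%: 0.95^3 = 0.857, or 69 of 80. If all of the two-year dropout fell before month 6, 0.9 x 0.857 = 0.772, or 62 of 80.

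**3. Change score against baseline adjustment.** With equal SD before and after and baseline correlation r, the change-score variance is 2(1 - r) and the baseline-adjusted variance is 1 - r². Their ratio is (1 - r²) / [2(1 - r)] = (1 + r)/2. Power is for a comparison of means at one visit, 72 per arm, difference 0.4 SD.

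| r | Change | Adjusted | Ratio | Power, change | Power, adjusted |
|---|---|---|---|---|---|
| 0.4 | 1.20 | 0.84 | 0.70 | 59.1% | 74.5% |
| 0.5 | 1.00 | 0.75 | 0.75 | 67.0% | 79.1% |
| 0.7 | 0.60 | 0.51 | 0.85 | 87.3% | 91.9% |

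These are results for means. They indicate the size of the loss for a rank test on change but are not exact for it.

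**The case against.** Several stronger readings are tempting, and the article does not support them.

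- *None of the tests compares the arms.* Not so. The paragraph opens with the aim of comparing the two groups. Mann-Whitney does this, and so does repeated-measures ANOVA with an arm-by-time term. Only signed-rank does not.
- *Baseline is ignored.* A change score subtracts it. What is missing is covariate adjustment, and in a randomised comparison that costs precision without causing bias.
- *The investigators already treat within-arm results as a comparison.* The Discussion reports that a pilot frequency score "increased only in the EBTUR group, but not in the cTURBT group" and speculates on reasons. The same paragraph then says that no conclusion about the difference can yet be drawn. That disclaims the inference, so the pilot is weak evidence of how the trial will be read.
- *The article plans to delete incomplete patients.* It does not say so. Deletion is a property of the classical method it names.
- *Most patients will be lost, or half of trials will mislead.* The 10% dropout is the only stated rate. If missed visits cluster in those patients, about 72 of 80 remain complete. The 50% figure is the maximum of 2p(1 - p), not a typical value.
- *The data will pick the method.* The list may be a condensed menu by type of outcome. An article often leaves the pairing of test and outcome to the analysis plan.

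It is also fair that rank tests suit short ordinal items and skewed scores, where a normal-theory mixed model is not automatically better.

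The core survives these points. The tests are stated, not omitted, and an analysis plan that followed the sentence would carry over their limits.

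**Conclusion.** The point holds in a limited form and concerns secondary outcomes only. Signed-rank results cannot support a statement about EBTUR against cTURBT; the 16-50% range applies to common changes of 0.2-0.4 SD with 72 per arm, with the algebraic maximum as its upper end. The loss under classical repeated-measures ANOVA runs from slight (72 of 80 kept) to serious (45 of 80 at an assumed 5% missed per visit), and it is smaller for voiding charts. Leaving baseline unadjusted gives up a variance reduction of 15-30% at correlations of 0.7 down to 0.4. The change is worth making because it uses data already collected, but it does not threaten the trial: the primary RFS analysis and the sample size stand apart from it.

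**What to change.** In the Statistical analysis section, name one primary between-arm analysis for these outcomes: a mixed model for repeated measures using all available post-baseline visits, with arm, visit, arm-by-visit interaction, baseline score and the stratification factors (age, past history of NMIBC, multiplicity, tumor diameter). Report the between-arm difference with its confidence interval at the scheduled visits of each measure: 1, 3 and 6 months for voiding charts and every post-operative visit for questionnaires. Keep a rank-based between-arm test as sensitivity analysis for short ordinal or skewed scores. State that signed-rank results are descriptive only. Whether the per protocol set is the right population for these outcomes is a separate question, which this change does not settle.

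The cost is a few sentences of wording and modest programming, with no new data. The downside is a distributional assumption that fits single ordinal items less well, which the rank-based sensitivity analysis is there to check.
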